
### Interventions

#### Nonindividualized Receptive Music Therapy

Participants engage in daily 30-minute instrumental listening sessions curated by a certified music therapist. The music therapists hold a master’s degree or higher in music therapy with a minimum of 5 years of clinical experience in psychiatric settings. Track selection follows a standardized protocol based on the predefined affective trajectory framework (Figure 2), and the final track list for each participant is reviewed by a second member of the research team to verify adherence to the selection criteria. Selection adheres to the “ISO principle” of mood entrainment [35]. Music initially matches the participant’s current affect and gradually shifts toward an adaptive target state. Before treatment, participants complete the Short Test of Music Preferences-Revised (STOMP-R), which assesses liking for 23 musical styles grouped into 4 categories on a 1‐7 scale (1=dislike strongly; 7=like strongly) [36,37]. Based on prior site-specific data showing high preference for “Reflective & Complex” and “Upbeat & Conventional” styles, the therapist selects instrumental tracks while excluding lyrical content to minimize semantic processing. Each session comprises 6 to 10 excerpts ordered to follow a specific affective trajectory: (1) for MDD and GAD: The sequence guides affect upward (eg, calm and sad → warm → cheerful → relaxed; Figure 2A); (2) for PI: The sequence follows a biphasic trajectory. It initially elevates affect to reduce negative rumination, then progressively decreases tempo and complexity to facilitate sleep onset (Figure 2B).

**Figure 2. F2:**
[figure not shown]
Music affective trajectories used in nonindividualized receptive music therapy (**A**) Affective trajectory for participants with major depressive disorder or generalized anxiety disorder, showing a gradual upward shift in target emotional valence (low → higher → moderate and settled) across the 30-minute session. The x-axis represents session time (minutes 0‐30); the y-axis represents target arousal and valence level on a standardized scale (higher score indicates higher arousal and positive valence). (**B**) Biphasic affective trajectory for participants with primary insomnia (PI) showing a biphasic trajectory. The x-axis represents session time (minutes 0‐30); the y-axis represents target arousal level (higher score indicates higher arousal and positive valence). The trajectory features a gentle initial rise in affect to reduce negative cognitions, followed by a progressive taper (slower tempo, simplified rhythm and melody, increased repetition) to lower physiological arousal before sleep.

In addition to the listening intervention, participants in the nonindividualized arm complete a brief weekly music-experience questionnaire that mirrors the contact time and structure of the weekly preference assessment used in the IMT arm. This questionnaire records the participant’s listening experience, mood, and engagement but is not used to alter the curated track list; its purpose is to equate the 2 arms for participant–researcher contact and procedural engagement, thereby reducing differential attention and expectation effects.

#### IMT

IMT uses an artificial intelligence (AI)–enabled pipeline to tailor the interventions to weekly patient preferences. Before each week’s session, participants complete a preference questionnaire across 6 dimensions: emotion, style, intensity, instrumentation, variation, and tempo. These inputs are converted into standardized prompts for the Suno music platform (V4 model; API: sunoapi.org). For example, a selection of “calm, Western Classical, flute and piano and cello, slow tempo” is programmatically rendered into a specific generation prompt. The system generates 16 unique instrumental tracks, which the participant rates on a 1‐7 scale. The 8 highest-rated tracks are compiled into the 30-minute intervention set for that week. To ensure therapeutic consistency across participants, the AI-generated tracks are subject to predefined acoustic constraints. All generated tracks are required to be purely instrumental (lyrical content is excluded). Furthermore, key acoustic features, including tempo (beats per minute), spectral centroid, and rhythmic complexity, are logged for each generated track. The therapeutic structure of the IMT condition mirrors that of the nonindividualized arm in session duration (30 min daily), number of tracks per session (6 to 10 excerpts), and overall affective trajectory framework. The sole difference lies in the source of the musical material (AI-generated based on individual preferences vs therapist-curated from existing libraries). Participants are instructed to listen once daily in a quiet environment and to focus their attention on the auditory experience and the emotions it evokes. The playback interface displays the following guidance: “Please adjust your posture to feel relaxed and comfortable. Close your eyes and begin deep breathing. After the music begins, focus all your attention on the music and the feelings it evokes.”

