## Methods

### Study Design

The program comprises 4 sequential studies (Table 1 and Figure 1): 1 cross-sectional study, 2 prospective cohort studies, and 1 randomized controlled trial (RCT). The target populations are adults with mild-to-moderate major depressive disorder (MDD), generalized anxiety disorder (GAD), or primary insomnia (PI), as well as healthy controls. All studies use a common assessment framework including baseline demographics, clinical characteristics, symptom severity, and electroencephalography (EEG), with follow-up assessments at weeks 1, 2, 4, 6, and 8.

**Table 1. T1:** Study description of the individualized (receptive) music therapy research program.

Study	Description	Translational role
Study 1 (Cross-sectional)	A pilot study (n=20; 5 per group: MDD^a^, GAD^b^, PI^c^, and HC^d^) to characterize clinical features and EEG^e^ patterns across the target disorders and healthy controls. These findings will be benchmarked against prior literature to calibrate study procedures.	Findings will be used to calibrate assessment procedures, verify the feasibility of EEG protocols, and generate preliminary hypotheses regarding disorder-specific neurophysiological signatures to guide the analytical framework of subsequent studies.
Study 2 (Prospective Cohort)	An open-label evaluation (n=80; 20 per group: MDD, GAD, PI, and HC) of the efficacy and safety of 8-week nonindividualized receptive music therapy with concurrent EEG monitoring.	Establishes preliminary efficacy benchmarks and identifies EEG features associated with treatment response. These data serve as the reference standard against which the added benefit of individualization is evaluated in study 3.
Study 3 (Randomized Controlled Trial)	A pilot RCT^f^ (n=300; MDD, GAD, and PI) in which participants are randomized 1:1 to receive either nonindividualized receptive music therapy or IMT^g^ for 8 weeks.	Provides the first direct comparison of individualized versus nonindividualized approaches. Clinical and EEG data from studies 1‐3 are pooled to develop a treatment-response prediction model.

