**Figure 1. F1:**
[figure not shown]
Study flowchart. MDD: major depressive disorder; GAD: generalized anxiety disorder; PI: primary insomnia; non-indiv: nonindividualized; EEG: electroencephalography.

The 4 studies are designed as a sequential translational pipeline in which each stage builds upon the preceding one. Study 1 serves as an exploratory pilot to calibrate clinical and EEG assessment procedures, verify protocol feasibility, and generate preliminary hypotheses regarding disorder-specific neurophysiological features. Although the sample size (n=20) is insufficient for definitive biomarker identification, this study provides essential groundwork for refining the measurement framework used in subsequent stages. Study 2 then evaluates the efficacy and safety of nonindividualized receptive music therapy in a larger cohort, establishing the clinical and neurophysiological benchmarks against which the individualized intervention will be compared. Study 3 directly compares the 2 approaches in a randomized controlled framework, enabling assessment of the incremental benefit of AI-enabled personalization. Finally, study 4 validates a treatment-response prediction model developed from the cumulative data of studies 1 through 3; this study is distinct from study 2 in that all participants receive IMT and the primary objective is to evaluate predictive accuracy rather than treatment efficacy per se.

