### Randomization and Blinding

For the RCT, an independent biostatistician will generate the allocation sequence using SAS software (version 9.4; SAS Institute). Randomization will be managed via a secure, web-based system to ensure allocation concealment. Upon confirmation of eligibility and completion of baseline assessments, the system will release the assignment to a research nurse who is not involved in outcome assessment. Outcome assessors will remain blinded to group assignment throughout the trial. Given the nature of the intervention, complete participant blinding is not feasible, as those in the IMT arm engage in weekly preference assessments and music selection, whereas participants in the nonindividualized arm receive therapist-curated tracks without weekly customization. Beyond the impossibility of participant blinding, we explicitly recognize that the weekly preference assessment and track-rating procedure in the IMT arm constitutes an additional, potentially active, component of participant–researcher interaction and engagement that is not present in a conventional nonindividualized protocol. Any between-arm difference in outcomes could therefore reflect not only the personalization of the musical stimulus itself but also this greater attention, engagement, and sense of agency. To mitigate both expectation bias and this attention and engagement confound, several strategies are used: (1) participants in both arms are informed only that they will receive music therapy, without being told which approach is hypothesized to be superior; (2) all participants complete equivalent contact time and daily listening schedules; specifically, participants in the nonindividualized arm complete a weekly music-experience questionnaire covering their listening experience, mood, and engagement, that is matched to the IMT arm’s weekly preference assessment in length, frequency, mode of administration, and degree of staff contact, so that the 2 arms are equated for attention and procedural engagement and differ only in whether the questionnaire responses are used to regenerate the following week’s music; and (3) primary outcomes are assessed by independent raters who have no knowledge of treatment allocation. In addition, to render expectation effects measurable rather than merely assumed, all participants complete a validated treatment-credibility and outcome-expectancy measure (the Credibility/Expectancy Questionnaire, CEQ) after allocation and before the first session; baseline expectancy scores will be compared between arms and entered as a covariate in prespecified sensitivity analyses of the primary outcomes. To assess the integrity of assessor blinding and to characterize residual participant unblinding, both participants and outcome assessors will be asked to guess the participant’s allocation at week 8, and a blinding index (bang blinding index) will be computed and reported. Unblinding of assessors is permitted only in the event of a medical emergency.

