#### Primary Outcome Analysis

For the response rate at 8 weeks, between-group comparisons will be conducted using chi-square tests, with results reported as risk difference and risk ratio with corresponding 95% CIs. To accommodate the repeated-measures structure of the data (assessments at baseline and at weeks 1, 2, 4, 6, and 8), linear mixed-effects models for repeated measures (MMRM) will be used for continuous outcomes, with fixed effects for treatment group, time, and their interaction; baseline scores will be included as covariates; and random intercepts for participants will be specified to accommodate within-subject correlation. Because study 3 cannot blind participants and the IMT arm involves additional engagement, 2 prespecified sensitivity analyses will probe the robustness of the primary treatment effect to expectation and attention effects: (1) the MMRM and the response-rate models will be refitted with baseline CEQ scores added as covariates; and (2) the analyses will be repeated with adjustment for the Bang Blinding Index to explore whether the estimated treatment effect is attenuated after accounting for residual unblinding. Concordance between the primary (unadjusted) and these expectancy-adjusted estimates will be interpreted as evidence regarding the extent to which any observed benefit is attributable to personalization of the stimulus rather than to differential expectancy or attention. Time to response or remission will be compared between groups using Kaplan–Meier survival curves and the log-rank test. For study 3, the primary analysis will follow an intention-to-treat principle, including all randomized participants according to their assigned group. A supplementary per-protocol analysis will include only participants who complete at least 80% of scheduled listening sessions (ie, a minimum of 45 of 56 daily sessions).

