
### Future Directions

If the pilot RCT demonstrates promising results, a fully powered, multicenter definitive trial will be warranted to confirm the efficacy of IMT across diverse clinical populations. To disentangle the personalization effect from the additional attention and engagement inherent in the IMT procedure, the definitive trial should consider a 3-arm design that adds an attention-matched sham-personalization control (in which participants complete weekly preference ratings but receive nonindividualized music), enabling the specific contribution of stimulus personalization to be isolated. Future studies should also incorporate longer follow-up periods (eg, 12 to 24 wk) to assess the durability of therapeutic effects and the potential for relapse prevention. Adequately powered, diagnosis-stratified samples will be required to draw firm disorder-specific conclusions for MDD, GAD, and PI, and to support confirmatory neurophysiological inference. The prediction model developed in study 4, if validated, could serve as a clinical decision-support tool for identifying patients most likely to benefit from individualized interventions; further refinement using machine-learning approaches with larger datasets would enhance its generalizability. Additionally, the integration of multimodal neuroimaging (combining EEG with fMRI or fNIRS) in future protocols could provide a more comprehensive understanding of the neural circuits engaged by IMT. Finally, investigating the applicability of the IMT framework to other psychiatric conditions, as well as to pediatric and geriatric populations, represents an important direction for extending the reach of this approach.

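### Study 3 changes the source of the music and its tailoring together, so it can test the IMT package but cannot attribute a benefit to personalization

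*Protocol article*

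**What the plan says.** The IMT section states: "The sole difference lies in the source of the musical material (AI-generated based on individual preferences vs therapist-curated from existing libraries". IMT music comes from a generative platform prompted by a weekly preference questionnaire. The participant rates 16 tracks, and "The 8 highest-rated tracks are compiled into the 30-minute intervention set for that week". Control music is chosen by a certified music therapist from a curated library, and the control arm's weekly questionnaire does not change the track list (Nonindividualized Receptive Music Therapy; Intervention Fidelity and Adherence Monitoring).

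Randomization and Blinding describes the contrast differently. After the attention-matched questionnaire, the two arms are said to "differ only in whether the questionnaire responses are used to regenerate" the next week's music.

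The role given to study 3 also varies. In Table 1, the study 2 data are "the reference standard against which the added benefit of individualization is evaluated in study 3", and study 3 "Provides the first direct comparison of individualized versus nonindividualized approaches". The design text below Figure 1 speaks instead of "enabling assessment of the incremental benefit of AI-enabled personalization".

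Primary Outcome Analysis plans to compare the unadjusted estimate with estimates adjusted for expectancy and blinding. Agreement is to be read as evidence on how far any benefit is "attributable to personalization of the stimulus rather than to differential expectancy or attention". Strengths and Limitations concedes that personalization is confounded with attention and expectancy. It does not mention the source of the music.

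**The concern.** The difference described as single has two parts. One is the origin of the music: a generative model, or existing recordings picked by a therapist. The other is whether the participant's weekly preferences drive what is played. The trial has no arm with AI-generated music that is not tailored, and none with library music tailored weekly.

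At stake is the meaning of the result. If generated tracks work less well than therapist-chosen recordings, a real benefit of tailoring could be hidden and a null result read as showing that individualization adds nothing. If generated tracks work better for reasons unrelated to preference, the gain would be credited to personalization. The result is meant to inform the definitive trial, so a misattribution would be carried forward.

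**Working it through.** **Inputs.** Two arms, randomized 1:1, n=300 (Table 1); 50 per arm per disorder (Sample Size Calculation), so 3 × 50 = 150 per arm. Assumed control response 70% and threshold of clinical importance 20 points (Sample Size Calculation). The plan gives no figure for the effect of musical source, so there is no figure of its own to reproduce on this point.

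**Step 1. What moves with arm.**

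| Feature | IMT | Control |
|---|---|---|
| Origin of the music | AI-generated | existing library, therapist-curated |
| Weekly answers change the music | yes | no |
| Participant rates tracks and the best are kept | yes, 8 of 16 | no |
| Weekly questionnaire and contact time | yes | matched |

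The first row is missing from the account in Randomization and Blinding. Control music is never generated, so there is nothing in that arm to regenerate. The two sections cannot both be right about what the sole difference is.

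**Step 2. What the contrast estimates.** Let μ(source, tailoring) be the response rate in each cell of a two-by-two layout, with L for library music, and 1 or 0 for weekly tailoring or none. Define

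- P = μ(L,1) − μ(L,0), the tailoring effect
- A = μ(AI,0) − μ(L,0), the source effect
- I = μ(AI,1) − μ(AI,0) − μ(L,1) + μ(L,0), their interaction

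The trial observes only μ(AI,1) and μ(L,0). Adding the three definitions gives μ(AI,1) − μ(L,0) = P + A + I. That is one estimable number for up to three unknowns.

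**Step 3. Whether a planned analysis can split it.** An indicator for AI source equals the IMT indicator for all 300 participants, so the two cannot enter one model. On the risk-difference scale, fit response on arm and the baseline Credibility/Expectancy Questionnaire (CEQ) score. Then

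unadjusted effect − adjusted effect = c × δ,

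where c is the CEQ coefficient and δ is the arm difference in mean CEQ. P and A do not appear separately. If c × δ is near zero the two estimates agree, and both equal P + A + I whatever the split. Agreement therefore says that measured expectancy does not explain the difference. It does not favour tailoring over source. Allocation guesses measure belief about assignment, not the origin of the music, so the blinding-index analysis does not help either.

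**Step 4. Illustration.** Assume control response 70%, IMT response 90% and I = 0, so P = 20 − A. The values of A are assumptions.

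| A (points) | P (points) | AI, untailored | Library, tailored | IMT − control |
|---|---|---|---|---|
| −5 | 25 | 65% | 95% | 20 |
| 0 | 20 | 70% | 90% | 20 |
| 10 | 10 | 80% | 80% | 20 |
| 20 | 0 | 90% | 70% | 20 |

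The trial's data would look the same in all four rows, because neither middle cell is observed. A larger sample narrows the interval around P + A + I and leaves the split unknown.

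**The case against.** The strongest reply is that the protocol is testing a package and largely says so. IMT is introduced as AI-enabled, the design text below Figure 1 refers to "enabling assessment of the incremental benefit of AI-enabled personalization", and the hypothesis in Principal Findings is about tailoring by means of generative AI. The IMT section states both attributes openly. A first comparison of a package is a legitimate design. This stands, and it is why the randomized comparison is not in doubt.

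Second, Primary Outcome Analysis sets personalization against two named rivals and speaks of evidence on the extent of attribution. A reader might infer a rule that assigns concordant estimates to personalization; the text is softer than that. But it names personalization as what is left once expectancy and attention are set aside, and musical source would be left equally.

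Third, the sentence in Randomization and Blinding may have been meant for the questionnaire procedure alone. As written, its subject is the two arms.

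Fourth, a reader might infer that controls receive no individual matching at all. The documents do not support that: music starts from the participant's current affect, each participant has a reviewed track list, and music preferences are measured before treatment. This makes the control less purely nonindividualized, but does not separate source from arm.

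Fifth, the acoustic screening, the therapist's weekly review of about 20% of generated tracks, and the choice of each participant's best-rated tracks make poor AI output less likely. They limit one direction of the source effect without removing it.

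**Conclusion.** Study 3 validly estimates the effect of the whole IMT package against therapist-curated library music. It cannot say how much of that effect is due to personalization, and no planned analysis changes this. Three places in the text need correction: the account of the arms in Randomization and Blinding, which contradicts the IMT section; the concordance inference in Primary Outcome Analysis, which goes beyond the design; and Strengths and Limitations, which omits musical source.

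The conclusion follows from the two-arm layout and rests on no assumed effect. The size of any misattribution cannot be derived from the documents, and the table of splits is illustrative only.

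A reader might also infer that the three-arm trial suggested in Future Directions, described as "enabling the specific contribution of stimulus personalization to be isolated", must fail in the same way. The text does not say whether its sham-personalization arm would receive AI or library music, so that cannot be concluded, and the suggestion concerns a later trial.

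**What to change.** 1. In Study Design (Table 1), Randomization and Blinding, IMT, and Primary Outcome Analysis, define the study 3 contrast as the IMT package (AI-generated, preference-based music) versus therapist-curated library music. Reconcile the account of the arms in Randomization and Blinding with that in the IMT section.
2. In Primary Outcome Analysis, keep the sensitivity analyses but limit the inference from concordance to robustness of the package effect against measured expectancy and unblinding. Make no attribution to personalization.
3. In Strengths and Limitations, add the source of the music (AI-generated versus therapist-curated) as a confound that cannot be separated from personalization in this trial.
4. Optionally, state in Future Directions that a sham-personalization arm isolates personalization only if its music comes from the same AI pipeline.

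Reporting the acoustic features of control tracks beside those logged for IMT tracks would describe the arms but not resolve the point, since those features differ by preference as well as by source.

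The cost is wording only. Treatment, enrolment, sample size and the primary analysis stay as they are. The downside is a narrower conclusion from study 3.
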